### Randomization

Randomization and allocation of participants to the two groups were done in advance by an independent researcher (CR) by means of a web-based program (https://www.sealedenvelope.com/) using permuted block randomization with variable block sizes of 2, 4, and 6 (randomly arranged) and a ratio of 1:1. Participants are stratified by center. The centers involved are two orthopedic clinics in southwestern Germany where recruitment is conducted consecutively. Participants are given randomly generated treatment allocations within sealed opaque envelopes. Once a participant is consented to participate in the study, the envelope is opened, and the patient is then offered the allocated treatment regimen. An independent researcher (CR) prepares the envelopes and is responsible for the allocation of participants to trial arms.

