### Statistical analyses

The primary outcome of physical activity assessed with the respective subscale of the BSA-F at T4 (post-treatment of MoVo-App) will be analyzed as a dependent variable and its baseline value as a covariate, adjusted for sex and age and potentially other covariates. Continuous secondary outcomes will be analyzed accordingly. The statistical analysis for all research questions will be based on linear mixed-effects models with restricted maximum likelihood estimation to account for missing data [71]. The model is a mixture model, thus assuming two distinct distributions: (1) a binomial model (patients becoming physically active from inactivity and vice versa) and (2) a Gaussian distribution of minutes of physical activity per week for those being physically active. In the linear mixed-effects models, time (T1 to T5) will be the within-subjects factor, and intervention (MoVo-LISA and TAU plus MoVo-App vs. MoVo-LISA and TAU) will be the between-subjects factor. All two-way interactions will be considered. Main effects and interactions will be estimated for time points T3 to T5.

Baseline minutes of sport activity, age, sex, and body mass index will be included as covariates, along with other relevant demographic and clinical characteristics (e.g., disease, pain intensity, pain interference) collected through patient self-report. The model will allow for random intercepts, and all other factors will be treated as fixed effects. All statistical analyses will be performed using R software [72].

We expect to see a skewed distribution in our primary outcome physical activity, and, following guidance [72, 73], we will use transformations or consider using generalized or mixture-distribution mixed models [72]. Effects will be considered significant if *p* < 0.05. Assumptions for general, generalized, or mixture-distribution models will be checked graphically and with tests appropriate to the model [74, 75]. In addition, we will run several model checks by comparing increasingly complex models with different covariance structures, link functions, and estimation procedures with a null model via likelihood ratio tests and comparison of fit via the Akaike information criterion and Schwartz’s Bayesian information criterion [76].

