To assess the mediating and moderating effects of psychosocial factors, the linear mixed-effects model of repeated measures will be extended by including psychosocial factors as random effect covariates. Their added effect as covariates, their interaction with IG, and a three-way interaction with IG and time will be estimated. It will be considered whether and how psychosocial intermediary effects depend on the intervention. Effects will be considered significant if *p* < 0.05.

The analysis does not consider a cluster effect of using two sites for the intervention. This decision is based on the high standardization in the delivery of the intervention and all study procedures in both sites. Differences in patient population between clinics will be accounted for by including demographic and clinical variables as covariates in the analysis. Furthermore, clinic was also used as a stratification factor in the randomization scheme (as detailed above).

Standardized mean differences and 95% confidence intervals will be calculated to measure the between-group effect size at post-treatment (T3) and follow-up (T4, T5). All analyses will be performed on an intention-to-treat basis. Completer (per-protocol) analyses will be conducted to investigate the influence of study attrition on study results. In addition, we will analyze the extent to which participants adhere to physical activity in accordance with the National Recommendations for Physical Activity and Physical Activity Promotion [77].

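### Clinic is a stratification factor in the randomisation but is left out of the model, and the stratification is cited in support; for the T4 group contrast this costs some precision

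*Protocol article*

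**What the plan says.** The Randomization section of the protocol article describes allocation "using permuted block randomization with variable block sizes of 2, 4, and 6 (randomly arranged) and a ratio of 1:1", and adds: "Participants are stratified by center". There are two centres.

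The Statistical analyses section then makes an explicit decision: "The analysis does not consider a cluster effect of using two sites for the intervention". It gives three reasons:

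- Standardisation: "This decision is based on the high standardization in the delivery of the intervention and all study procedures in both sites".
- Patient covariates: "Differences in patient population between clinics will be accounted for by including demographic and clinical variables as covariates in the analysis".
- The design itself: "clinic was also used as a stratification factor in the randomization scheme".

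The covariates named in the same section are patient characteristics: "Baseline minutes of sport activity, age, sex, and body mass index will be included as covariates", together with other demographic and clinical variables that patients report themselves. Clinic is not among them, and the random part of the model is described only as random intercepts, with no site term named.

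**The concern.** Blocking within clinic keeps the arms nearly balanced in each clinic, so differences between clinics largely drop out of the treatment comparison. An analysis without clinic does not use this. It still counts the between-clinic variation as noise, and its standard error describes a less efficient design than the one that was run. The stratification cited in the plan is therefore an argument for a clinic term.

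The other two reasons do not replace that term. Standardised delivery limits differences in how the programme is given, but the outcome is sport done at home six months after discharge. The sections on MoVo-LISA and on treatment as usual say that each clinic's own therapists deliver the programme and that care after discharge may vary and follows no protocol. Patient covariates address differences in case mix only.

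At stake is precision: a confidence interval somewhat too wide and a test somewhat conservative for the between-group contrast at T4.

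**Working it through.** The plan gives no between-clinic variance and no calculation on this point, so there is no figure of its own to reproduce. The check asks what omitting clinic does under a stated range.

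**Inputs**
- From the Randomization section: two clinics, 1:1 allocation, permuted blocks of 2, 4 and 6 within clinic.
- From the sample size section: 224 patients, 15% dropout and a pre-post correlation of 0.33. Completers: 224 × 0.85 = 190.4, taken as 190, or 95 per arm.
- Assumed: a two-sided 5% test, and a share *s* of the variance left after the patient covariates that lies between clinics, with *s* = 0, 2%, 5% and 10%.

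**Formulas for the linear T4 contrast**

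Let σ² be the residual variance without clinic and *n* = 95.
- Standard error reported without clinic: σ√(2/n).
- Actual standard error, because blocking nearly removes the between-clinic part: σ√(2(1−s)/n).
- Ratio: 1/√(1−s).
- Actual two-sided error rate: 2[1 − Φ(1.96/√(1−s))].
- Equivalent loss of patients: 190 × s.

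| s | SE ratio | 1.96/√(1−s) | Actual error rate | Patients |
|---|---|---|---|---|
| 0 | 1.000 | 1.960 | 5.0% | 0 |
| 2% | 1.010 | 1.980 | 4.8% | 3.8 |
| 5% | 1.026 | 2.011 | 4.4% | 9.5 |
| 10% | 1.054 | 2.066 | 3.9% | 19 |

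**Simulation with the trial's block scheme** (two equal clinics, 190 patients, correlation 0.33, 10,000 runs per setting). The rejection rate under no effect, without and with a fixed clinic term, was:
- s = 0: 0.048 and 0.048
- s = 2%: 0.050 and 0.054
- s = 5%: 0.045 and 0.052
- s = 10%: 0.037 and 0.050

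The Monte Carlo standard error is √(0.05 × 0.95/10,000) = 0.0022. The 5% and 10% results agree with the formula. At 2% the simulation cannot tell the formula's 4.8% from 5%.

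**Group-by-time interaction.** A clinic difference that is constant over time is absorbed by the patient's random intercept and cancels from a within-patient contrast. In a simulation with 190 patients, two equal clinics, three time points and s = 10%, the interaction standard error was 0.1679 both without and with a fixed clinic term (ratio 1.000). In the same setting the between-group contrast at T4 gave a ratio of 1.053, close to the 1.054 above.

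**Binomial part (active or inactive).** The formula does not carry over. In logistic regression, omitting a prognostic stratum pulls the treatment coefficient towards zero, and the standard error becomes smaller. With an assumed clinic log-odds of 1.2, a simulation gave a standard error of 0.298 without clinic and 0.313 with it. The consequence is attenuation and some loss of power.

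**The case against.** The strongest reply is that the effect may be negligible. Both clinics are in southwestern Germany, one team trained all instructors in the same two-day course, and entry is limited to patients with under 30 minutes of sport a week. The share that matters is what remains after baseline minutes, age, sex, body mass index and the clinical covariates, and that could be close to zero. This stands: the documents give no between-clinic variance, and the range above is an assumption.

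A second reply is that the plan rejects only a cluster effect, and that with two sites a random site effect is indeed not worth fitting. That is right about the random effect. It does not supply the missing fixed effect, since the plan offers patient covariates in its place. Nor is this a detail that a condensed article leaves to a fuller document: it is a stated decision with stated reasons.

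A third reply is that the sample size section ties its smaller effect, d = 0.35, to the group-by-time interaction, where a constant clinic difference cancels. This also stands and limits the point. It does not remove it, because the Statistical analyses section also specifies the T4 value as dependent variable with baseline as a covariate, and that is a comparison between patients.

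A reader might infer that leaving out the sites biases the effect or raises the false-positive rate, as ignoring clusters does in a cluster-randomised trial. The documents do not support this: patients are randomised individually within clinic, so in the linear part the error is on the conservative side.

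A reader might also infer that the omission worsens a shortage of power. That does not follow either. The sample size section gives two effects, d = 0.62 for the main effect and d = 0.35 for the interaction. The interaction, with the smaller effect, is the quantity that the omission hardly touches. Whether 224 patients suffice is a separate question on which this point does not rest.

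**Conclusion.** The point holds in a limited form. The plan stratifies by clinic, leaves clinic out, and cites stratification as support when it is a reason to adjust.

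For the linear between-group contrast at T4, the standard error is overstated by 1.0% to 2.6% if clinic explains 2% to 5% of the variance left after the patient covariates, and by 5.4% at 10%. The actual error rate is then about 4.8% to 4.4%, or 3.9% at 10%. These figures assume 190 completers, near balance within clinic and a two-sided 5% test. If clinic does not predict outcome, there is no loss.

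The linear treatment estimate is not biased. The group-by-time interaction is largely unaffected by a constant clinic difference. In the binomial part the consequence is an attenuated coefficient and some loss of power, not an inflated standard error. No conclusion of the trial becomes unsafe. This is an efficiency gain that costs almost nothing, and it also corrects a wrong argument.

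**What to change.** Replace the paragraph on the two sites in the Statistical analyses section with:

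> Clinic (two levels, the stratification factor) is included as a fixed effect in the primary model, in both the binomial and the Gaussian part, and in all secondary models; no random site effect is fitted because there are only two sites.

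The patient covariates stay as planned. The cost is one sentence and one degree of freedom in each part of the model. No new data are needed, since each patient's clinic is known from the randomisation. The protocol version is dated June 2020 and first results are expected in 2021, so at that date the change could still be recorded before the analysis.

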### Ethical considerations

Participants eligible for the study receive detailed study information and are asked for their participation (informed consent). Smartphone-based interventions have proved to be effective in a variety of RCTs without clinically meaningful side effects being reported yet [28, 78]. Due to the focus on patients with musculoskeletal conditions, the participants are at an increased risk of injury compared with the general population. The medical suitability of participants for the intervention is recorded continuously as part of the inpatient rehabilitation diagnostic assessment and treatment. Data security and confidentiality are guaranteed under the General Data Protection Regulation Act. A data security concept is created together with the data security department at the University of Freiburg, Germany. Central ethical approval has been confirmed from the Albert Ludwig University of Freiburg (DRKS00014814).

## Discussion

The present trial focuses on individuals with musculoskeletal conditions. The purpose of the MoVo-App trial is to evaluate a blended intervention of inpatient, face-to-face treatment coupled with a mobile app to help initiate and promote the maintenance of physical activity in this vulnerable patient group. Previous studies have shown that the initial adoption of physical activity is possible and successful in this population. Most studies to date have not succeeded in implementing long-term habit change in participants.

In a rigorous evaluation, this trial addresses some of the gaps of prior studies. First, given that many people have busy lifestyles, they value convenient access to health behavior change programs [79]. In this context, the MoVo-App offers the opportunity to support behavioral interventions in real-life situations. Second, although apps have a high potential to support individuals to become active more sustainably, most of the apps are lacking evidence-based content [80]. In the development of the MoVo-App, we systematically translated the theoretical concepts of the MoVo process model into the app. Third, outcomes in this study not only comprise physical activity behavior but also measure health-related variables (e.g., pain intensity, depression) and underlying psychological mediators of behavior change as postulated within the MoVo concept. This will allow a deeper understanding of the treatment processes within MoVo-LISA and the MoVo-App, which in turn can help to further develop the intervention. Fourth, by implementing the intervention directly into routine healthcare, we will be able to enroll a more naturalistic sample. Most trials of internet- and mobile app–based interventions suffer from a selection bias with mostly highly educated and female participants self-selecting into these interventions [35, 81]. Due to the consecutive routine care sample, self-selection bias can be minimized in this trial. Finally, MoVo-LISA is conceptualized to be used for a wide range of settings and indications. Therefore, the blended intervention of MoVo-LISA and the MoVo-App can easily be transferred to other (healthcare) settings as well as health conditions.

Some limitations need to be addressed. First, the primary outcome is assessed with a questionnaire that is only available in German and does not provide a minimal clinically important difference. Second, there are no objective measures of the primary outcome physical activity conducted. If the results of this study indicate that the blended intervention of MoVo-LISA and MoVo-App is more effective than MoVo-LISA alone, its clinical impact on the promotion and maintenance of an increased level of physical activity could be substantial.

## Trial status

This is protocol version number 3, dated June 04, 2020. Recruitment began on 7 January 2019; the last patient was enrolled on 3 December 2019. The first results of this study are expected in 2021.

## Data Availability

The final dataset, excluding any demographic and personal information allowing identification of participants, and the statistical analysis code will be accessible from the corresponding author upon reasonable request.

## Abbreviations

BPI: Brief Pain Inventory
BSA-F: Movement and Sport Activity Questionnaire
CONSORT: Consolidated Standards of Reporting Trials
CSQ-I: Client Satisfaction Questionnaire adapted to Internet-based interventions
DRKS: German Clinical Studies Trial Register
ICD-10: International Statistical Classification of Diseases and Related Health Problems, 10th Revision
IG: Intervention group
MoVo: Motivation-Volition concept
MoVo-LISA: Motivation-Volition concept to support Lifestyle-Integrated Sports Activity
MoVo-App: MoVo-based smartphone application
RCT: Randomized controlled trial
SPIRIT: Standard Protocol Items: Recommendations for Interventional Trials
TAU: Treatment as usual
